## Abstract

**Objective:**

To evaluate the effectiveness of pelvic floor muscle training (PFMT) on pelvic floor muscle (PFM) function and quality of life (QoL) in women with stress urinary incontinence (SUI) and pelvic organ prolapse (POP).

**Methods:**

This study will be a randomized, controlled, parallel, and blinded clinical trial. The final sample will consist of 32 women diagnosed with SUI and cystocele (stage I and II). All volunteers will be assessed and reassessed using the same protocol: assessment form, gynecological examination, functional evaluation of PFM, and questionnaires to assess quality of life, urinary function, and sexual function. All volunteers will be evaluated for satisfaction levels post-treatment. The intervention will be PFMT, totaling 16 sessions to be conducted twice a week. Reevaluation will take place at the end of treatment and 1 month after completion of PFMT. Descriptive analysis and repeated measures ANOVA will be used for result analysis. A significance level of p<0.05 will be considered for all statistical tests.

**Ethics and dissemination:**

This study has been submitted to the Ethics in Research Committee of the Federal University of Rio Grande do Norte and approved under protocol number 5.826.563. It has been registered with the Brazilian Clinical Trials Registry ReBec (RBR-49p6g3t). It is expected that these studies will provide a deeper understanding of the efficacy of PFMT in women with SUI and cystocele. Additionally, it aims to provide more insights into the efficacy of PFMT prior to surgery.

## Introduction

Among the various forms of urinary incontinence (UI), stress urinary incontinence (SUI), characterized by the involuntary loss of urine during activities that increase intra-abdominal pressure [1], is the most prevalent, affecting 25% to 45% of women, depending on the population [2]. SUI can occur in conjunction with pelvic organ prolapse (POP). Around 55% of women with stage II POP report urinary loss [3, 4]. POP´s complex origin involves risk factors like pregnancy, childbirth, connective tissue issues, aging, and PFM weakness, among others [5–8].

The anterior vaginal compartment POP, also known as cystocele, is the most frequent type of POP [9–11]. Women diagnosed with cystocele may experience various symptoms in the pelvic floor region, including a sensation of pelvic heaviness, vaginal protrusion, difficulty with urination, and sexual dysfunction [10–13]. A study [14] demonstrated that women with cystocele and/or the absence of the urethrovesical sulcus were 2.5 times more likely to experience UI.

Several studies have already established the negative impacts of both POP and UI on various aspects of women’s lives, encompassing social, occupational, domestic, psychological, physical, and sexual well-being [15–17]. Pelvic Floor Muscle Training (PFMT) has garnered Level A evidence for improving the symptoms of SUI [18, 19], enabling conscious and effective contractions [19–21] which yield positive benefits in terms of pelvic floor strength, function, and quality of life (QoL) [18, 19].

However, the clinical outcomes and cost-effectiveness relationship of PFMT in POP management remains unclear. A systematic review conducted by Cochrane [13] identified only one study involving elderly women engaged in ground exercises and health education. The review concluded that while some evidence suggests ground exercises may be beneficial for certain types of prolapse, randomized controlled trials are needed to evaluate the effectiveness of PFMT for POP treatment.

Currently, studies evaluating the efficacy of PFMT in women with genital prolapse encompass various types of POP [22–31]. A single study [32] explored PFMT for cystocele. However, the intersection of SUI and cystocele within PFMT remains unexplored. Considering that PFMT is the preferred initial treatment for incontinent women [19, 20], due to its non-invasive nature, cost-effectiveness, and minimal complications compared to surgery [14, 33], the hypothesis arises that women with SUI and cystocele could benefit from PFMT. Thus, this study aims to evaluate the effectiveness of PFMT in enhancing PFM function and the QoL in women with SUI and cystocele.

## Methodology

### Study design and research site

A controlled, randomized, parallel, and blinded clinical trial will be conducted at the Maternidade Escola Januário Cicco (MEJC) in Natal, Rio Grande do Norte, Brazil. This study has been registered with the Brazilian Clinical Trials Registry ReBec (RBR-49p6g3t) and received approval from UFRN’s Research Ethics Committee in December 19, 2022 (protocol 5,826,563). Data will be stored in the Department of Physiotherapy at the Universidade Federal do Rio Grande do Norte (UFRN) and will be archived with the principal investigator for 5 years. After this period, the data will be discarded.

### Eligibility criteria

Women with stress urinary incontinence (SUI), identified using the International Consultation on Incontinence Questionnaire—Short Form (ICIQ-SF), and a diagnosis of cystocele at stage I and II according to the Pelvic Organ Prolapse Quantification System (POP-Q) scale [34, 35] will be recruited. The participants’ age range will be between 18 and 65 years, not in menopause, and without a history of gynecological surgeries related to SUI, POP, or hysterectomy. Patients lacking cognitive capacity to comprehend and respond to the questionnaires as determined by the assessor, those with vaginal bleeding, current diagnosis of urinary tract infection, neoplasms, and/or those who decide not to continue participating in the study or withdraw their consent will be excluded.

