### Results

All assessments will be conducted by a blinded evaluator. The volunteers will undergo initial evaluation, including medical history, gynecological examination, functional assessment of the PFM, and questionnaires. The assessments will take place at three time points: before treatment (baseline assessment), at the end (final assessment), and one month after the last session (re-assessment). Fig 7 illustrates the assessment and re-assessment items.

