### Sample size

The sample size was pre-determined using G-Power 3.1.9.2 (F-tests—ANOVA: repeated measures, between groups), based on a previous study [46] utilizing vaginal manometry data. The sample size was estimated with a significance level of 0.05, power of 98%, and effect size of 0.23. According to this methodology, the sample size resulted in 27 participants. An additional 20% for possible losses (5 volunteers) was added. Thus, 32 volunteers will be recruited and randomized into two groups of 16 participants each.

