### Adverse effects

Adverse effects of PFMT are rare. Any discomfort or pain linked to treatment will be assessed. Volunteers will be closely monitored, asked about session discomfort, and adverse events documented. If risks arise, interventions halt. Withdrawn participants still factor into intention-to-treat analysis.

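### The eligibility criteria exclude women who stop or withdraw, with no limit to the time before randomisation, while the adverse-effects section keeps withdrawn women in the intention-to-treat analysis

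*Protocol article*

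**What the plan says.** Two sections of the protocol article deal with women who do not complete the study.

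- **Eligibility criteria.** After baseline conditions such as bleeding, infection and neoplasm, the same sentence adds that "those who decide not to continue participating in the study or withdraw their consent will be excluded". It gives no time limit and does not say whether the woman leaves participation, follow-up or the analysis.
- **Adverse effects.** After describing how discomfort is monitored and when interventions halt, the section closes with "Withdrawn participants still factor into intention-to-treat analysis".

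The Statistical analysis section gives the tests, the sphericity correction and the significance level. It names no analysis set and has no rule for withdrawals.

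Losses are expected. Under Sample size, "the sample size resulted in 27 participants", then "An additional 20% for possible losses (5 volunteers) was added", so that "32 volunteers will be recruited and randomized into two groups of 16 participants each". Outcomes are measured repeatedly: "The assessments will take place at three time points", namely baseline, end of treatment and one month after the last session (section headed Results).

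**The concern.** Deciding not to continue is something a woman can do after she has been allocated, so it does not belong without qualification in a list of baseline exclusions. Applied to randomised women, the clause makes membership of the analysis depend on a post-allocation event, and the groups compared are no longer those that randomisation formed.

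This matters more here than in a trial with similar arms. Under Interventions, the training group attends 16 sessions over two months and the comparator group has one information visit. Rates of stopping and reasons for stopping may well differ between such arms.

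There is also a practical risk. A conventional repeated-measures ANOVA, the named analysis, uses only women with all measurements. If the text is left as it is, the smaller set could arise by default while the report describes the analysis as intention-to-treat, or the set could be chosen after the results are seen.

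**Working it through.** **1. The two statements side by side**

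| | Eligibility criteria | Adverse effects |
|---|---|---|
| Who | women who stop or who withdraw consent | withdrawn women |
| What happens | excluded | counted in intention-to-treat |
| Timing stated | none | none, but the context is treatment under way |

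The overlap is the woman who is randomised and then withdraws. On the literal reading of the first section she is out; under the second she is in. The Statistical analysis section does not decide between them.

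**2. Size of the analysis set**

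Inputs, all from Sample size: 27 before losses, 20% for losses, 32 randomised, 16 per arm.

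- The plan's own figure: 27 × 0.20 = 5.4, taken as 5; 27 + 5 = 32. This agrees with the stated total. The 27 is taken as given here, and nothing below depends on how it was derived.
- All randomised women analysed: 32.
- Literal exclusion, if the 5 planned losses are all women who stop or withdraw: 32 − 5 = 27.
- Difference: 5/32 = 15.6% of those randomised.

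**3. Illustration of bias**

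Assumption, not in the document: in each arm, stoppers' mean change in pressure is δ = 0.5 SD below that of stayers. With k stoppers among 16, the all-randomised mean is the stayers' mean minus (k/16) × δ. Dropping stoppers therefore overstates that arm's mean by (k/16) × δ. The bias in the difference, training minus control, is

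(k_training − k_control)/16 × δ.

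| Losses, training / control | Bias (SD of change) |
|---|---|
| 3 / 2 | (3 − 2)/16 × 0.5 = 0.03 |
| 4 / 1 | (4 − 1)/16 × 0.5 = 0.09 |
| 5 / 0 | (5 − 0)/16 × 0.5 = 0.16 |

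If the split is reversed, the sign reverses: 2 / 3 gives −0.03 and 0 / 5 gives −0.16.

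**4. Can this be expressed as a share of the planned difference?**

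The plan gives "significance level of 0.05, power of 98%, and effect size of 0.23" for "F-tests—ANOVA: repeated measures, between groups". Taking the extreme value, 5/16 × 0.5 = 0.156 SD:

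- 0.23 read as Cohen's f: d = 2 × 0.23 = 0.46, and 0.156/0.46 = 0.34. This treats the SD of change as equal to the SD of a single measurement, which holds only at a correlation of 0.5.
- The same reading with an assumed correlation of 0.8: the SD of change is √(2 × 0.2) = 0.63 of the measurement SD, and 0.156 × 0.63/0.46 = 0.21.
- 0.23 read as f² (the Statistical analysis section uses f² for its effect size): f = √0.23 = 0.48, d = 0.96, and 0.156/0.96 = 0.16, again with the two SDs treated as equal.

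The share moves from 0.16 to 0.34 on readings that the document does not settle, and that is for the extreme split alone.

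**The case against.** The strongest reply is that the two sections can be read together. Being excluded, in an eligibility section, may mean only that the woman leaves participation, or that she declines between consent or baseline assessment and allocation. Neither would remove a randomised woman from the analysis. The Adverse effects sentence is the only one that speaks of analysing withdrawn women, it states the intention-to-treat principle, and no per-protocol or completers rule appears elsewhere. This stands in part: a reader might infer that the two statements cannot both be followed, but that is true only on the literal reading. What remains is that the clause carries no such limit and no other section supplies one.

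A reader might also infer that the bias favours training. Women who gain little may stop training, but women who improve early may stop too, and unimproved controls may not return. The document gives no stopping rates or reasons by arm, so the direction is plausible at most.

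Finally, a condensed article may leave details of follow-up after stopping, and of missing outcomes, to a fuller protocol or a statistical analysis plan that is not shown. That is fair, and their absence is not the point. The point is two statements in the text that do not agree as worded.

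**Conclusion.** The point holds as an unreconciled conflict of wording with a possible effect on the primary comparison. Read literally, the eligibility clause would leave 27 of 32 randomised women in the analysis at the planned 5 losses, provided that all of these losses are women who stop or withdraw. With an assumed deficit of 0.5 SD in stoppers in both arms, the bias towards training is about 0.03 SD for a 3 / 2 split and 0.16 SD if all 5 losses fall in the training arm. Losses mainly among controls would turn it the other way.

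It is tempting to say that exclusion would inflate the effect by about a third of the planned difference. The document does not support this. That figure takes the most extreme split, mixes the SD of change with the SD of a measurement, and assumes that 0.23 is Cohen's f. No fixed share should be quoted.

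This should be fixed. It falls short of a defect that invalidates the plan, because the intended principle is already stated and a milder reading of the clause is available.

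**What to change.** 1. In Eligibility criteria, delete the clause on stopping and withdrawal, or limit it to women who decline before randomisation.
2. In Statistical analysis, state once that all randomised women are analysed in their allocated group, and let the Adverse effects section refer to that statement.
3. In the same place, state that women who stop sessions are still invited to the two planned follow-up assessments, and that data collected before withdrawal of consent are kept unless the woman also withdraws consent to their use.

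The cost is wording in two or three places and a few follow-up invitations. The sample size and the outcomes do not change. Follow-up should be settled early, because assessments that are not made when a woman stops cannot be recovered at analysis.

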### Ethics and disclosure

The participants will be fully informed about objectives, procedures, and voluntary participation, in accordance with Resolution No. 466/12 and the Declaration of Helsinki. Participants’ consent will be obtained through signed informed consent forms. Confidentiality of personal information is ensured throughout and after the study.

The database will be provided as part of the manuscript and its supporting information will be deposited in the journal’s repository. In addition to the database, statistical data, including means, medians, and measures of variance, will also be available.

### Participant schedule

The participant schedule is described in Fig 1.

**Fig 1 pone.0308701.g001:**
[figure not shown]
Participant schedule. **Note:** ICIQ-SF: International Consultation on Incontinence Questionnaire—Short Form; ICIQ-OAB: International Consultation on Incontinence Questionnaire Overactive; PFDI-20: Pelvic Floor Distress Inventory; WHOQOL: World Health Organization Quality of Life; FSFI: Function Sexual Female Index; PGI-C: Patient Global Impression of Change.

### Interventions

The intervention will involve individualized care, randomly divided into two groups: pelvic floor muscle training group (PFMTG) and comparator group (CG). The CG will receive informational content only, provided by a healthcare professional with expertise in urogynecology during a single visit. The educational material will encompass informative content about urinary incontinence, its risk factors, pelvic floor anatomy and function, types of UI, bladder and bowel functioning information, along with the significance of healthy lifestyle habits.

The PFMTG will receive similar educational material as the CG and will undergo 16 sessions conducted twice a week, totaling 2 months of treatment. The treatment for this group will encompass four exercise modalities: warm-up, breathing exercises, abdominal exercises, and pelvic mobility exercises. All exercises will involve pelvic floor muscle (PFM) activation. Progressions will be incorporated into each modality throughout the training.

In general, the breathing, abdominal, and pelvic mobility exercises will consist of two sets of eight repetitions during the first four weeks, progressing to three sets of eight repetitions in the final four weeks, except for the transversus contraction and plank exercises.

The PFMTG intervention will have an average duration of 45 minutes per session, with the initial five minutes dedicated to warm-up, 30 minutes for exercise execution, and approximately 10 minutes allocated to intervals between exercises.

#### Warm-up

During the initial eight sessions, participants will perform five quick contractions and five sustained slow contractions of the PFM for 3 seconds, three cough simulations associated with PFM contraction, and eight plantar flexions also linked with PFM contraction (Fig 2). In the subsequent eight sessions, the number of quick and slow PFM contractions will remain the same, while cough simulations will increase to five, and plantar flexions will be raised to 12. The rest period between each exercise will be 1 minute.

**Fig 2 pone.0308701.g002:**
[figure not shown]
Warm-up exercises. (A) Position for quick and slow contractions of the pelvic floor muscles; (B) Cough associated with contraction of the pelvic floor muscles; (C) Bipodal position with external hip rotation and plantar flexion, involving the contraction of the pelvic floor muscles. Illustration by [name].

#### Breathing exercises

Participants will perform the diaphragmatic breathing exercises associated with PFM contractions at the time of expiration. The progression of this modality will happen by changing the postures in which is executed, as shown in Fig 3. The participant will progress in this modality every four sessions.

**Fig 3 pone.0308701.g003:**
[figure not shown]
Progression of diaphragmatic breathing exercises associated with pelvic floor muscle contraction. (A) Supine position; (B) Sitting position; (C) Standing position; (D) Sitting position with the assistance of a Swiss ball, the upper limb on the same side as the ball positioned over it in a hugging manner, and the hand of the contralateral limb resting on the lateral region of the ribs on that side.

#### Abdominal exercises

*a) Transversus contraction*. During the initial four sessions, transversus contraction will be performed in a supine position, with the instruction to "draw the navel towards the spine" along with forced exhalation.

In the final 12 sessions, the participant will perform a prone plank position on the support of knees and elbows, as show in Fig 4. Initially, the participant will hold the position for five seconds, with an additional five seconds to each subsequent session, ending with 60 seconds on the support. PFM contraction will be prompted every five seconds during the plank. Thus, in the first session, the participant will perform one contraction, and by the end, 12 contractions will be completed.

**Fig 4 pone.0308701.g004:**
[figure not shown]
Progression of transverse muscle contraction exercises associated with pelvic floor muscle contraction. (A) Supine position; (B) Plank position. Illustration by [name].

*b) Bridge*. Bridge exercise will be conducted in a supine position with support on the mat. The PFM contraction will occur at the start of the hip elevation movement and continue until they return to the initial position. Progression will occur through position changes (Fig 5).

**Fig 5 pone.0308701.g005:**
[figure not shown]
Progression of bridge exercises associated with pelvic floor muscle contraction. (A) Bridge position with bipodal support; (B) Bridge position with unipodal support; (C) Bridge position with bilateral support of lower limbs on the Swiss ball at calf height. Illustration by [name].

#### Pelvic mobility exercises

Pelvic mobility exercises will be performed in the directions of anterior and posterior tilt, with the PFM contraction prompted during the posterior tilt. Progression will be achieved through position changes (Fig 6).

**Fig 6 pone.0308701.g006:**
[figure not shown]
Progression of pelvic mobility exercises associated with pelvic floor muscle contractions. (A) Seated position on the Swiss ball; (B) Standing position; (C) Four-point kneeling position. Illustration by [name].

### Results

All assessments will be conducted by a blinded evaluator. The volunteers will undergo initial evaluation, including medical history, gynecological examination, functional assessment of the PFM, and questionnaires. The assessments will take place at three time points: before treatment (baseline assessment), at the end (final assessment), and one month after the last session (re-assessment). Fig 7 illustrates the assessment and re-assessment items.

**Fig 7 pone.0308701.g007:**
[figure not shown]
Assessment and re-assessment items. **Note:** ICIQ-SF—International Consultation on Incontinence Questionnaire; ICIQ-OAB—International Consultation on Incontinence Questionnaire Overactive; PFDI -20—Pelvic Floor Distress Inventory; WHOQOL-bref—World Health Organization Quality of Life; FSFI—Function Sexual Female Index; PGI-C—Patient Global Impression of Change.

The primary outcome will be PFM pressure measured by vaginal manometry. Secondary outcomes will include manual muscle strength testing (Modified Oxford Scale) and questionnaires: International Consultation on Incontinence Questionnaire—Short Form (ICIQ-SF), International Consultation on Incontinence Questionnaire Overactive (ICIQ-OAB), Pelvic Floor Distress Inventory (PFDI-20), World Health Organization Quality of Life (WHOQOL), Female Sexual Function Index (FSFI), and Patient Global Impression of Change (PGI-C).

#### Vaginal manometry

The pressure exerted by the PFM will be measured using the PeritronTM model 9300AV, achieved through a probe inserted into the vaginal canal. The value is given in cmH2O, thus representing an indirect measure of muscle strength [36]. For the examination, the volunteer will assume the lithotomy position. The volunteer will be instructed to perform three maximal contractions, with a 30-second interval between them [37], and instructed not to associate the PFM contraction with abdominal muscles, hip adductors, or glutes. The considered value will be the average of the three attempts and categorized based on pressure as very weak (7.5–14.5), weak (14.6–26.5), moderate (26.6–41.5), good (41.6–60.5), and strong (>60.6) [38].

#### Manual muscle strength testing

The evaluator performs bidigital palpation and instructs the volunteer to contract the PFM with the command "squeeze my finger with maximum force you can." It is necessary for the volunteer not to associate PFM contraction with accessory muscles. Muscle strength is graded according to the Modified Oxford Scale [39], which classifies muscle strength into six grades, from grade 0 to 5.

